#### ***Professional and team level***

To account for the influence of department type on team climate and patient safety culture, we will analyse the before-and-after outcomes using a linear mixed model with the department type as a random effect. Since the professionals are almost the same in the before-and-after measurements, the difference scores in team climate and patient safety culture will be considered as dependent variables.

#### ***Departmental level***

The paired *t*-test (by department) will be used on the percentage of observed patient safety data collected during safety walk arounds to measure difference in patient safety on departments before and after auditing.

### Process evaluation

We will carry out the process evaluation to explain the effects. We will determine the components of internal auditing or factors other than auditing that could have influenced patient safety. We will document the different audit steps and the participation level of the healthcare providers (physicians, nurses, and allied healthcare workers) and department leaders. We will also measure the experience of these healthcare providers and department leaders with the auditing (level 1 of Kirkpatrick’s theory [27]) in an online survey, which has been tested and reviewed by experts for face validity. The survey will be e-mailed to those who participate in the audit within 2 weeks after the audit. Non-respondents will receive one reminder. According to the Kirkpatrick’s theory, the degree of exposure is equal to the extent that healthcare providers and leaders are familiar with auditing and have learned during auditing (level 2) and the way they have adapted their behaviour to improve patient safety (level 3). Semi-structured interviews will be used to measure the level of learning, behaviour change, and the related facilitators and barriers. Purposive sampling will be used to select a varied group of healthcare providers and department leaders [43]. We expect that 24 interviews will be enough to reach the point of theoretical saturation. If not, additional interviews will take place until no new information about the experiences with the audit system appears. An interview guide will be developed to facilitate these interviews. The interviews will be audio-taped and transcribed according to a standardised format. Atlas.ti.6 will be used for the qualitative analysis. We will study any changes in the safety policy and the number and type of implemented safety interventions after the audits by analysing audit reports, improvement plans, and revisit reports.

### Ethical approval and principles

The Ethical Committee of the Radboud University Nijmegen Medical Centre (RUNMC) approved the study on 11 July 2011. It conforms to Dutch law and privacy regulations and was judged not to involve human-subject research. The manuscript was registered on 12 March 2012 in the Dutch Trial Registry for clinical trials. The Dutch Trial Registration record number is NTR3343.

The participation of hospital departments in the study is voluntary. The researcher gave an oral presentation and written information to each department head about the consequences of participating in the study. Written consent has been obtained from all participating departments of the hospital. The data will be separated from the names of the participants (departments, healthcare providers, and patients) and published anonymously. Each participant will be identified in the database with a number and an identity code. These codes are available only to the researchers and the research assistant.

## Discussion

We evaluate the effects of patient safety auditing in hospital care. This study is relevant for hospitals that intend to use early detection of unsafe care and to improve patient safety continuously. Our study provides a better understanding of how auditing can help improve patient safety.

This study has several strengths and limitations. Most patient safety interventions, including auditing, are complex interventions because they often consist of multiple parts (multicomponent) and aim at several levels of the health pyramid (multilevel) and various actors (multitargeted) [44]. Therefore, we set up a mixed-method evaluation study in which we combine qualitative and quantitative measurement instruments to measure several outcomes at different levels: the patient, professional, and departmental levels. We use widely applied and thoroughly studied instruments to measure adverse events, patient experiences, team work, and patient safety culture among healthcare providers [5,18,32,45].

The causal relationship between internal auditing and change in adverse event rates is difficult to identify because of the presence of other hospital initiatives to improve patient safety [44,46]. Therefore, we will carry out a process evaluation to analyse the mechanism and processes responsible for the outcomes of the effect evaluation. We use questionnaires and interviews to study the factors that facilitate or hinder the effectiveness of auditing. This is also important for giving recommendations to other hospitals that want to implement some or all of our audit system.

We will analyse time series data of SMRs and prolonged hospital stay for better evidence of cause-and-effect relationships. Possible underlying secular trends will be detected, and perhaps they will help explain some of the effects [47].

To improve the internal validity by reducing bias, the following actions are taken. To reduce selection bias, patients were randomly selected from the hospital database. All the care personnel in the department who are working in clinical care are invited to fill in the TCI and HSOPS. To prevent participant recall bias, we survey patients 3 months after hospital admission at the latest. The experiences of healthcare personnel and department leaders with the audit system are measured within 2 weeks after the auditing (survey) and 1 month after the revisiting (interviews).

To decrease response bias, non-respondents receive a reminder. Missing values in the medical record review are checked. Inter-rater agreement of retrospective assessments is measured and given back to the physician reviewers to improve the reliability of the assessment of adverse events and complications.

Information bias is reduced by having a research assistant enter the research data. The data will be separated from the names of the participants (departments, healthcare providers, and patients). Each participant will be identified in the database with a number and an identity code. These codes will be available only to the research assistant and researchers. An independent researcher will check the data entries. An independent statistician will check the analyses.

To prevent confounding bias, we will study potentially confounding determinants of the relationship of auditing and patient safety by means of regression analysis and time series analyses.

To prevent publication bias, the study has been registered in the Dutch register for clinical trials. Additionally, we have installed an external Advisory Board with the special tasks of checking the integrity of the study group and giving methodological feedback.

The generalisability of the study will be low because it is carried out in a single hospital in a before-and-after design without concurrent controls. Ideally, the evaluation of the effects of auditing on hospital care should be studied in a large, multicentre trial with randomisation of hospitals with and without internal auditing [46,47]. Randomised controlled trials are the gold standard for evaluating healthcare interventions. A randomised, controlled, multicentre trial is not possible in this case. All Dutch hospitals have a legal obligation to systematically monitor, control, and improve the quality of care. Therefore, each one has some kind of auditing. However, for a hospital to temporarily refrain from a systematic analysis of quality assurance is unethical and illegal. Additionally, each hospital is unique in its management structure and the way internal auditing is performed. Therefore, a comparable control hospital with exactly the same management structure, organisation, and patient safety culture would be nigh impossible to find. We therefore decided to limit the evaluation of the effects of auditing on patient outcomes and professional practice to the one hospital that the other Dutch university hospitals regard as having the best practice for internal auditing [48]. Nevertheless, before-and-after designs are useful for studies that are part of local quality improvement projects such as audits, PDCA cycles, or action research [49]. In our circumstances, an evaluation of a local initiative in a before-and-after design is the only feasible option. This way of evaluating patient safety auditing with several measures and methods at different levels will provide the scientific proof we need for improving patient safety in hospitals.

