**Figure 1 F1:**
[figure not shown]
Audit components.

**Table 2 T2:** Methods and instruments used within the audit system

**Audit system**	**Methods**	**Instruments**
Measurements	Studying policy and quality indicators	Online self-assessment tool based on legal, national, and professional practice standards [16]
	Semi-structured interviews of health care providers	Standardised interview forms [17]
	Systematic observations (e.g. physicians’ discussions of complications and patient handovers)	Standardised observation forms [17]
	Questionnaire about team functioning of healthcare providers	Team Climate Inventory [18]
Feedback of audit findings by presentation and report	Patient record review to measure adverse events	Standardised record review form based on a protocol originally developed by the Harvard Medical Practice Study [19]
	Assessment of the quality of medical and nursing patient records	Standardised assessment forms [19,20]
	Appraisal of document management (e.g. protocols and procedures) and guideline adherence	Standardised assessment forms partly based on the AGREE instrument [21]
Follow-up: revisiting 15 months after the audit to monitor improvements	Appraisal and assessment of quality of consultation and collaboration by main internal and external partners	Standardised appraisal and assessment questionnaire [22]

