We will measure two patient safety indicators: SMR and prolonged hospital stay. The SMR is a method for comparing mortality ratios over time, or between subpopulations, taking into account the differences in population structure [39]. The ratio is of the observed to expected deaths, conventionally multiplied by 100. A prolonged hospital stay is the actual hospital stay of a clinically admitted patient that is more than 50% longer than expected [40]. A prolonged hospital stay takes into account the fact that patient stays tend to become prolonged after complications [41]. The SMR and hospital stay data are generated from the routine administrative data of the hospital.

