#### ***Patient level***

A logistic regression analysis will analyse changes in the rates of patient admissions with adverse events and complications between before-and-after measurements, while correcting for clustering on the hospital department level. The intra-class correlations, the ratio of the between group, and the total variance will be calculated. Since the patient records will be different in the before–and-after measurements, the effect of timing (i.e. auditing) will be accounted for with a fixed effect for time (dummy variable for the second measurement). The incidence rates of adverse events and complications will be calculated with 95% confidence intervals (CIs). The inter-rater agreement within pairs of physicians will be expressed as a kappa (K) statistic with 95% CIs and as a percentage of records that agree about the presence or absence of complications and adverse events.

A linear mixed model will be used to analyse the before-and-after outcomes of the quality of hospital care according to the patients. To account for the possibility that changes over time will be influenced by changes in patient mix, terms will be added to the model for age, sex, education, and self-reported general and mental health status. Since the patients will be different in the before-and-after measurements, the effect of the timing of the auditing will be accounted for with a fixed effect for time (dummy variable for the second and third measurements).

We will use a linear mixed model with a Poisson distribution for the SMR and prolonged hospital stay to compare the rates from baseline to the end of the initial 18-month evaluation period (3 months before and 15 months after auditing). We will adjust this model for patient and departmental characteristics.

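### SMR and prolonged stay are measured against expected values that fuller recording after the audit could raise, yet their series are offered as better causal evidence with no check on the expected part

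*Protocol article*

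**What the plan says.** The section on patient-level outcomes defines both administrative outcomes relative to an expectation. For the SMR, "The ratio is of the observed to expected deaths, conventionally multiplied by 100", and the measure is described as "taking into account the differences in population structure". For stay, "A prolonged hospital stay is the actual hospital stay of a clinically admitted patient that is more than 50% longer than expected". On the source: "The SMR and hospital stay data are generated from the routine administrative data of the hospital".

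The patient-level part of the statistical analyses compares both measures in a Poisson mixed model over the period from 3 months before to 15 months after the audit, and adds: "We will adjust this model for patient and departmental characteristics". The article names no analysis of observed deaths, actual stay or the expected values on their own.

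Table 2 lists, among the audit's methods, "Assessment of the quality of medical and nursing patient records", and among its stages, "Feedback of audit findings by presentation and report". The text on the audit procedure adds that the department head then draws up and carries out an improvement plan based on the audit report and the board's priorities.

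The Discussion gives these two series a particular role: "We will analyse time series data of SMRs and prolonged hospital stay for better evidence of cause-and-effect relationships". The safeguard it names for them is the detection of underlying secular trends.

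**The concern.** An outcome defined against an expected value can improve in two ways: patients fare better, or the expectation rises. Here the intervention may act on the second. The audit examines record quality and reports on it to the department. If that leads to more complete recording of diagnoses and comorbidity, and if those items enter the expected deaths and expected stay, then the SMR and the share of prolonged stays both fall although nothing has changed for patients.

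Such a change would follow the audit department by department, so it would have the timing that a monthly series is meant to detect. It is not a secular trend, and looking for one would not reveal it. Adjustment for patient characteristics would not remove it if those characteristics come from the same records, and the article does not give their source. At stake is the reading of a fall in either measure as evidence that the audit made care safer.

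**Working it through.** The article states no power or precision for these two outcomes, so there is no planned figure to reproduce. The check holds patient outcomes fixed and raises only the expected values.

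**Inputs from the article (Table 4 and the patient-level analysis section)**
- Deaths in the eight departments in 2012: 233.
- Prolonged stays in the eight departments in 2012: 3268.
- Evaluation period: 3 months before and 15 months after the audit.
- Threshold for a prolonged stay: actual stay above 1.5 times expected.

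**Assumptions (not in the article)**
- Expected values rise by x = 5% or 10% through fuller recording.
- The SMR starts at 100.
- Actual/expected stay is lognormal with mean 1 and log-SD s of 0.6, 0.8 or 1.0.
- The 2012 counts serve as annual rates pooled over departments, with pure Poisson variance unless stated.

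**SMR**
- SMR after = 100/(1+x): 100/1.05 = 95.2; 100/1.10 = 90.9.
- Deaths: 233 × 3/12 = 58.25 before; 233 × 15/12 = 291.25 after.
- SE of the log rate ratio = √(1/58.25 + 1/291.25) = 0.144.
- z = ln(1+x)/SE: 0.0488/0.144 = 0.34 for 5%; 0.0953/0.144 = 0.66 for 10%.

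**Prolonged stay**
- Share prolonged = 1 − Φ((ln(1.5(1+x)) + s²/2)/s), with x = 0 before.

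| s | Before | x = 5% | Change | x = 10% | Change |
|---|---|---|---|---|---|
| 0.6 | 16.5% | 14.5% | −11.8% | 12.8% | −22.1% |
| 0.8 | 18.2% | 16.7% | −8.6% | 15.3% | −16.3% |
| 1.0 | 18.3% | 17.0% | −6.9% | 15.9% | −13.2% |

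- Counts: 3268 × 3/12 = 817 before; 3268 × 15/12 = 4085 after.
- SE of the log rate ratio = √(1/817 + 1/4085) = 0.0383.
- z for x = 5%: at s = 0.6, −ln(0.882)/0.0383 = 3.3; at s = 1.0, −ln(0.931)/0.0383 = 1.9.
- If the variance doubles (overdispersion, variation between departments), divide by √2: 3.26/1.414 = 2.3 and 1.87/1.414 = 1.3.

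The two outcomes therefore behave differently. The SMR estimate would be biased, but the shift is small against its sampling error. Prolonged stay has about 14 times as many events (3268/233), and a threshold measure reacts more than proportionally to a shift in the expectation. A modest recording change could be enough there.

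**The case against.** The strongest objection is that the mechanism needs two links that the article does not supply. It does not say that expected deaths or expected stay use recorded diagnoses; for the SMR it mentions only population structure. Nor does it say that the audit changes coding in the administrative database, as opposed to assessing medical and nursing records. The inputs may well be given in the full protocol, and their absence from an article is no fault. This stands, and it limits the point to a conditional risk. A reader might infer that the audit will inflate the expected values, or that any improvement in these measures would be false. The documents support neither.

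Second, the sizes rest on assumed rises and an assumed distribution, and the SMR shift is not distinguishable from noise. This also stands. A reader might treat both outcomes as equally likely to give a falsely significant result; the arithmetic does not bear that out. Nor need the change appear as a sharp step, since an improvement plan takes effect over time.

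Third, the article already concedes that causality is hard to establish and that there are no concurrent controls. It plans a process evaluation of improvement plans and of factors other than auditing. Both outcomes are secondary, and the primary outcome comes from record review without an expected value. All this lowers the stakes. But the process evaluation could at most show that recording improved. The article names no analysis that would divide a fall in either measure between recording and outcome, while the causal claim is attached to these two series.

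**Conclusion.** The point holds as a conditional risk to two secondary outcomes, and it justifies an inexpensive addition. It rests on the expected values depending on recorded diagnoses or comorbidity and on recording becoming fuller after the audit. If the expected values use age and sex only, there is no effect.

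Given those conditions, the prolonged-stay result is the exposed one: a 5% rise in expected stay could by itself approach or pass conventional significance, depending on the spread of stays and the true variance. For the SMR, the effect is a bias of about 5 to 9 points that would rarely be significant.

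A reader might go on to infer that a fall should count only if the expected part has not risen. That does not follow. If the case mix really worsens, the expected part should rise, and discounting the fall for that reason would defeat the purpose of standardising.

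**What to change.** In the patient-level part of the statistical analyses, keep the planned models and add two things:

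- Model and report by month the observed deaths per admission and the actual length of stay, beside the expected deaths and expected stay.
- Add one sensitivity analysis standardised only on items that recording practice cannot change, such as age, sex and acute or planned admission.

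In the Discussion, limit the causal reading of a fall in either measure when it comes mainly from a rise in the expected part and is absent in the sensitivity analysis. Do not require the expected part to stay level.

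The cost is a few extra tables and one further model on routine data. The drawback is cruder case-mix adjustment in the sensitivity analysis, which should therefore be read beside the main result and not in place of it.

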## Methods/design

### Study design and setting

The study is a mixed-method evaluation study with a before-and-after study design.

The study is taking place in a 953-bed university hospital in the Netherlands. Eight hospital departments have been included; namely, general surgery, neurosurgery, obstetrics and gynaecology, orthopaedics, pulmonary medicine, general internal medicine, cardiology, and paediatrics. Audit procedures were or are planned for these departments from October 2011 until April 2013. The departments were selected because of the estimated high risks of preventable adverse events. The selected departments reasonably represent the medical practice in Dutch hospitals. Outpatient care and one-day hospital stays are excluded.

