All of the 40 hospital departments that deliver or facilitate patient care are audited once every 4 years according to a fixed procedure and scheme. The auditing (Table 3) consists of nine steps (Figure 2). An independent Institute for Quality Assurance and Safety organises the audit procedures to ensure some kind of independence. To stress the independence of the institute: it is headed by a board of six representatives of physicians, nurses, allied healthcare workers, and healthcare researchers of the hospital. The audit team consists of five auditors, with at least one physician and one nurse. None have a direct relationship with the audited department. The chairman of the audit team is a medical department head of a contiguous specialism. Audit teams report audit findings to the board of the Institute for Quality Assurance and Safety. The board prioritises audit findings for the head of the audited department. The department head establishes and implements an improvement plan on the basis of the audit report and the prioritisation. The Board of Directors of the hospital controls the risk of unsafe care as indicated by means of the audit information and monitors the progress of improvement plans.

**Table 3 T3:** Terminology

**Term**	**Definition**
Internal auditing	An independent, objective assurance and consulting activity designed to add value and improve an organisation's operations. It helps an organisation accomplish its objectives by bringing a systematic, disciplined approach to evaluating and improving the effectiveness of risk management, control, and governance [10]*.*
Audit process	A set of established methods for conducting the audit of a department. It describes the activities of auditors needed to achieve the audit objectives [23].
Audit team	A group of experienced, trained, and knowledgeable individuals selected to perform an internal audit. The audit team is responsible for auditing selected departments in its own hospital [23].
Auditee	The department or employee of the department being audited [23].

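### For SMR and prolonged stay, the before-and-after design is not the only feasible one: staggered audit dates and monthly routine data allow a within-hospital comparison in the same calendar months

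*Protocol article*

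**What the plan says.** The Discussion rules out a randomised multicentre trial on legal and ethical grounds. It then rules out a control hospital, because "a comparable control hospital with exactly the same management structure, organisation, and patient safety culture would be nigh impossible to find", and concludes: "In our circumstances, an evaluation of a local initiative in a before-and-after design is the only feasible option". It acknowledges that "it is carried out in a single hospital in a before-and-after design without concurrent controls", but gives this as a reason for low generalisability.

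Other sections describe the setting:

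- Study design and setting: "Eight hospital departments have been included", and "Audit procedures were or are planned for these departments from October 2011 until April 2013".
- Auditing of patient safety: "All of the 40 hospital departments that deliver or facilitate patient care are audited once every 4 years", on a fixed scheme.
- Outcomes and Table 4: SMR and prolonged stay are produced monthly from routine administrative data and are labelled time series.
- Statistical analyses, Patient level: these two outcomes get a Poisson mixed model comparing 3 months before with 15 months after auditing, adjusted for patient and departmental characteristics. No concurrent comparator is named.
- Discussion: "The causal relationship between internal auditing and change in adverse event rates is difficult to identify because of the presence of other hospital initiatives". Time series analyses are promised to detect secular trends and to address confounding, without a stated method.

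**The concern.** The reasons given exclude a control hospital and the withholding of audits. They do not exclude comparing departments of the same hospital that were audited at different times. That comparison withholds and delays nothing, and for the two monthly outcomes the data come from a system the hospital already runs.

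The main threat that the article itself names is other safety initiatives in the hospital. A contrast aligned on time since audit cannot separate such a change from the audit when the after-period lies later in calendar time than the before-period. A trend seen only in the audited departments' own series does not settle it either. A concurrent comparator bears directly on this threat, which concerns internal validity and not only generalisability.

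**Working it through.** The article gives no precision figure for these two outcomes (its 7% concerns record review), so there is no planned figure to reproduce.

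**Inputs from the article.** Eight departments; audits from October 2011 to April 2013 (18 months from first to last); study end July 2014; 233 deaths and 3268 prolonged stays in the eight departments in 2012 (Table 4); 40 departments on a 48-month cycle.

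**Assumptions.** Evenly spaced audits, equal event rates across departments, Poisson variation, and an even hospital-wide audit schedule. Individual audit dates are not given.

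**1. Is there a concurrent comparator?** From October 2011 to March 2013 there are 8 × 18 = 144 department-months. With even spacing the mean wait from October 2011 to audit is 9 months, so 8 × 9 = 72 are not yet audited. Only 21 of these (7 departments × 3 months) lie in the planned 3-month before-windows. For the rest of the hospital, 40/48 = 0.83 audits a month gives about 15 audits in the 18 months (25 of 40 departments not audited then) and about 28 in the 34 months to July 2014 (12 not audited).

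**2. Steady background decline.** The midpoints of the before- and after-periods lie 15/2 + 3/2 = 9 months apart. With no audit effect, the apparent rate ratio is (1 − annual decline)^(9/12):

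- 2% a year: 0.985
- 5% a year: 0.962
- 10% a year: 0.924

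**3. One-time hospital-wide fall of 10%.** With the same 3:15 window in every department, the estimate is the pooled after-rate divided by the pooled before-rate. The worst date is close to the sixth audit, 12.86 months after the first. By then the share of after-time following the fall is (0.143 + 0.314 + 0.486 + 0.657 + 0.829 + 3)/8 = 0.679. The share of before-time following it is (0.857 + 1)/8 = 0.232. The apparent ratio is (1 − 0.0679)/(1 − 0.0232) = 0.954, a reduction of about 4.6%. Rounding audit dates to whole months gives up to about 4.8%: 81 of 120 after-months and 5 of 24 before-months, so 0.9325/0.9792 = 0.952. Other dates give less.

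**4. Precision.** Planned contrast, deaths: 233/12 × 3 = 58.25 before and 233/12 × 15 = 291.25 after, so SE of the log ratio = √(1/58.25 + 1/291.25) = 0.144. Prolonged stay: √(1/817 + 1/4085) = 0.038. The other rows come from the Poisson information matrix with department effects, calendar-month effects where stated, and a single audit term.

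| Model and data | Deaths | Prolonged stay |
|---|---|---|
| Planned −3/+15 contrast | 0.144 | 0.038 |
| Same window, calendar-month effects | 0.205 | 0.055 |
| All months July 2011 to July 2014, no month effects | 0.085 | 0.023 |
| All months, calendar-month effects | 0.146 | 0.039 |
| All months, month effects, plus 8 comparison departments of equal volume (assumption) | 0.104 | 0.028 |

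**5. Form of the audit effect.** Suppose the rate ratio falls evenly on the log scale to 0.80 at month 15. Its average over k = 1 to 15 of 0.80^(k/15) is about 0.89. Fitted to expected counts without background change, the planned contrast returns 0.89. A single on/off audit term with calendar-month effects on the eight departments alone returns 0.94 with 36 pre-audit months and 1.01 in the planned window. With 10 comparison departments and 36 pre-audit months it returns about 0.89.

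**The case against.** The strongest case for the plan is that it does not ignore the problem. It labels these outcomes time series, promises trend analysis, states that attribution is difficult and admits that controls are lacking. The exact time terms may stand in an analysis plan that is not shown. That stands, and the absence of a calendar term from the article is not in itself the point. The point is that the article declares that no other design is feasible, and that the promised analyses supply no concurrent comparator.

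The comparison departments are also uncertain. A reader might infer that the hospital has unaudited departments to use as controls. It does not: all 40 are on the cycle, and the others are only departments not audited in a given window. Their dates are not given. Some only facilitate care and may have no inpatients. Of the eight study departments the article says: "The departments were selected because of the estimated high risks of preventable adverse events". Department effects do not correct for different trends. This stands as a limit on the extra departments; the staggering among the eight remains.

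A reader might also infer that calendar adjustment is free. In the planned window it raises the SE for deaths by 43% (0.205/0.144). On all months it gives 0.146 against 0.085 unadjusted. It only roughly matches the planned SE because more months are used.

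Finally, a simple on/off model could mislead more than the planned contrast if the effect builds slowly (step 5). That is likely here, since the audit works through a report, an improvement plan and a revisit at 15 months. This stands and shapes the fix.

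**Conclusion.** The claim that only a before-and-after design is feasible is too strong for SMR and prolonged stay. The article's own schedule and data allow a within-hospital comparison, and the stated contrast leaves part of any hospital-wide change inside the audit effect. The size is moderate: an apparent rate ratio of about 0.96 or 0.92 for a background decline of 5% or 10% a year, and at most about a 4.6% apparent reduction for a single 10% fall. For prolonged stay, with a planned SE of 0.038, a spurious log ratio of ln 0.924 = −0.079 is about two standard errors. For deaths it is about half of one.

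A reader might infer that a hospital-wide fall would appear in full as an audit effect. The article's staggered windows do not support that: full appearance would need the fall to coincide with each department's own audit.

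The figures rest on evenly spaced audits and equal department volumes. Staggering itself is inferred from the 18-month span. The point concerns two secondary outcomes. Adverse events and complications are measured only at −3 and +15 months and gain little.

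**What to change.** Keep the planned contrast. For SMR and prolonged stay, add a Poisson model with department effects, calendar-time effects and an audit effect that may build with time since audit, not a single on/off step. Use the full monthly series of the eight departments. Where audit dates and inpatient volumes allow, add other inpatient departments not audited in the window, and report results with and without them. Series reaching back much further need care: 36 months before the first audit is October 2008, before the 2009 changes to the audit process in Table 1.

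Withdraw the only-feasible-option claim for these two outcomes, and describe the record-review and survey results as before-after changes.

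Costs: a wider routine-data extract; a larger SE than an unadjusted contrast on the same data, and an effect allowed to build up will be less precise than the single-term figures above; possible differences in trend between the high-risk eight and other departments; and no gain for the primary outcomes. No audit has to be moved or withheld.
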